### Randomization method and intervention process

Eligible participants will be randomly divided into treatments with either double placebo, vitamin D alone, omega-3 alone, or double active (vitamin D and omega-3) groups according to the stratified block randomization. Block randomization is done in equal block sizes of four to ensure balance between groups. Stratified randomization will be used to control serum vitamin D level (vitamin D < 20 ng/mL, range = 20–32 ng/mL) [28] distribution. Any individual who is not involved in trial data collection and analysis carries out randomization. The intervention allocation will be blinded to the study investigators, participants, and the statistical analyzer.

Zahravi Pharmaceutical Company (Tabriz, Iran) produced vitamin D and omega-3 supplements and placebos. This was approved by the Food and Drug Administration. The appearance of the placebo capsule was indistinguishable in color, shape, size, packaging, smell, and taste from vitamin D and omega-3 capsules. The type of supplements in each group will be blinded as A, B, C, and D packages for investigators, participants, and the statistical analyzer.

Participants will receive supplements in four groups for eight weeks:
Vitamin D placebo every two weeks + 1000 mg omega-3 containing 360 mg eicosapentaenoic acid (EPA) and 240 mg docosahexaenoic acid (DHA) twice a day;50,000 IU vitamin D every two weeks + omega-3 placebo twice a day;50,000 IU vitamin D every two weeks + 1000 mg omega-3 twice a day;Vitamin D placebo every two weeks + omega-3 placebo twice a day.

At the beginning of the study, participants will receive the supplements. Previous studies have not reported any side effects from the supplements [22, 23]. Compliance of the participant to the intervention will be measured using capsule count and capsule log record. Their potential complications and consumption processes will be registered (number of consumed capsules and the returned packages). In addition, the consumption process will be checked once a week by telephone and any occurrence of adverse events will be recorded. Participants will be asked to keep their usual lifestyle including nutrition and physical activity level (Additional file 1).

### Study outcomes

#### Primary outcomes

The primary outcome of this clinical trial is the difference in FBS in eight weeks between double placebo, vitamin D, omega-3, and double active groups from baseline to the post-intervention visit.

#### Secondary outcomes

The secondary outcomes of this clinical trial are changes in other glycemic indices, lipid profiles, psychological distress, anthropometric indices, and blood pressure at the end of the study in comparison with the baseline values.

### Assessments and measurements

Participants will be visited at the Shahid Rastravesh Health Center three times, at baseline, after three days and after eight weeks. Participants will be interviewed regarding their sociodemographic background at baseline.

Then, at the beginning and eight weeks after the intervention, the following will be done:
Blood sample will be drawn after at least 12 h of fasting. All blood samples will be centrifuged at 3000 rpm for 10 min and serum will be separated into clean tube aliquots and stored at – 80 °C until analysis [12]. Collection of blood, specimen storage, and laboratory tests will be conducted at the Shahid Rastravesh Health Center laboratory in Karaj. To determine FBS, serum triglycerides, TC, and HDL-C concentrations, we will use an enzymatic kit (Pars Azmun, Tehran, Iran). LDL-C will be estimated based on the Friedewald equation [27]. Serum level of vitamin D and insulin will be quantified using a commercial enzyme-linked immunosorbent assay kit (Monobind, CA, USA).The HOMA-IR and HOMA-B will be determined according to suggested formulas [29].

$$ \mathrm{HOMA}-\mathrm{IR}=\left[\mathrm{FBI}\ \left(\upmu \mathrm{U}/\mathrm{mL}\right)\mathrm{x}\ \mathrm{FBS}\ \left(\mathrm{mg}/\mathrm{ml}\right)\right]/405 $$
$$ \mathrm{HOMA}-\mathrm{B}=\left[\mathrm{FBI}\ \left(\upmu \mathrm{U}/\mathrm{mL}\right)\ \mathrm{x}\ 360/\mathrm{FBS}\ \left(\mathrm{mg}/\mathrm{ml}\right)-63\right]\% $$
Weight, height, and waist circumference will be determined using a digital scale, stadiometer, and non-elastic tape, respectively. They are measured thus: weight without shoes, with minimal clothing, and with a 100-g accuracy (Beurer, BF220, Germany); height without shoes, standing, heels against the wall, flat and forward head, and with 0.5-cm accuracy (Seca, Hamburg, Germany); and waist circumference with minimal clothing, midway between the last rib and the iliac crest. BMI will be calculated using the height and weight measurements kg/m^2^ [12].Systolic and diastolic blood pressure values will be measured with a digital manometer (Beurer, Germany). Values will be recorded in mmHg [30] .Physical activity will be investigated the short form of IPAQ [31]. The IPAQ form comprises walking, moderate intensity, and vigorous intensity activity and will be expressed as metabolic equivalents per minute (MET min) per week. The levels of physical activity will be categorized into low, moderate, and high based on the IPAQ criteria. This questionnaire has been validated in previous studies [32] including in Iran [33].Food intake status will be assessed using the three-day food records (comprising two working days and one weekend). Modified Nutritionist-4 software program (First Databank, San Bruno, CA, USA) will be used to estimate the energy and nutrient intakes.DASS-21 and PSQI will be applied to assess psychological distress [34, 35].DASS was designed to measure emotional distress in three subcategories [34] of depression (e.g. loss of self-esteem/incentives and depressed mood), anxiety (e.g. fear and anticipation of negative events), and stress (e.g. persistent state of over arousal and low frustration tolerance).DASS is a self-report scale with 21 items (seven items for each category) based on a 4-point rating scale. To calculate comparable scores with full DASS, each seven-item scale will be multiplied by two. Participants will be asked to explain times of occurrence of each item (in the form of statements) over the past week, with “0 = did not apply to me at all” to “3 = applied to me very much, or most of the time.” The higher score shows more severe emotional distress. Validity and reliability of the DASS-42 were examined in several studies and in Iranian samples [36–38].The PSQI is a self-report questionnaire that assesses sleep quality and quantity [35]. The19-item self-report questionnaire yields seven component scores: subjective sleep quality; sleep latency; sleep duration; habitual sleep efficiency; sleep disturbances; use of sleeping medication; and daytime disfunction.There are five additional questions. These are not used in the scoring. A Global Sleep Quality score > 5 indicates poor sleep quality. There is evidence of the reliability and validity of the PSQI in several subjects [39–42] and also in Iran [43, 44].

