## Methods/design

### Study design

This is an eight-week 2 × 2 factorial, triple-blinded (study investigators, participants, and statistical analyzer), randomized, placebo-controlled trial. Overall, 168 women of reproductive age diagnosed with prediabetes (fasting glucose 100–125 mg/mL) will be screened for enrolment in the study. This study will be conducted at Shahid Rastravesh Health Center Laboratory, Alborz University of Medical Sciences, Karaj, Iran.

Eligible participants who meet the inclusion and exclusion criteria will be randomly divided into four groups to receive double placebo (omega-3 and vitamin D placebos), omega-3 placebo and vitamin D supplement, omega-3 supplement and vitamin D placebo, and supplements of omega-3 and vitamin D.

In this factorial 2 × 2 design, we want to address five questions:
Compared to placebo, is omega-3 effective?Compared to placebo, is vitamin D effective?Are vitamin D + omega-3 more effective than placebo?Are vitamin D + omega-3 more effective than vitamin D alone?Are vitamin D + omega-3 more effective than omega-3 alone [24]?

Participants will visit the trial sites three times: at baseline (0 weeks); after three days; and post intervention (eight weeks after intervention). The flow chart of the study protocol is presented in Fig. 1.

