### Inclusion criteria

Women of reproductive age (aged 15–50 years);FBS 100–125 mg/mL [1, 2, 25];Vitamin D < 32 ng/mL [26];BMI < 30 kg/m^2^.

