### Study participants

Women of reproductive age with prediabetes from Karaj health centers diagnosed with FBS test (fasting glucose 100–125 mg/mL) [1, 25] will be invited to this study.

The study investigator will call participants by phone and will screen them according to the inclusion and exclusion criteria.

Eligible participants will be referred to the Shahid Rastravesh Health Center. First, the goals, methods, and benefits of the intervention will be explained by the investigator and the informed consent form will be signed by participants. At the beginning, 10 mL of blood will be taken from a peripheral vein after a 12-h overnight fast to assess plasma glucose levels, insulin, TG, HDL-C, TC, and vitamin D. After centrifuging for 10 min (3000 rpm), the serum samples will be frozen simultaneously and stored at − 80 °C until analyzed [12]. LDL-C will be estimated based on the Friedewald equation [27]. Participants will receive a three-day food record. The investigator will explain how to complete the form to each participant.

After three days, women who have been confirmed as having prediabetes (fasting glucose 100–125 mg/mL) and hypovitaminosis D (vitamin D < 32 ng/mL) [26] will be invited to the Shahid Rastravesh Health Center.

The sociodemographic characteristics questionnaire, short-form International Physical Activity Questionnaire (IPAQ), DASS-21, and PSQI will be completed with interviews. The investigator will review completed three-day food record in presence of each participant.

Anthropometry including weight, height, and waist circumference will be measured using a digital scale, stadiometer, and non-elastic tape, respectively.

Blood pressure (systolic and diastolic) will also be measured with a digital manometer.

All the above-mentioned stages, including blood sampling, completing four questionnaires (three-day food record, IPAQ, DASS-21, and PSQI), anthropometric measurements and measuring blood pressure, will be repeated after eight weeks.

At the end, the evaluated outcomes will be presented to participants privately. A Data Monitoring Committee (DMC) will also monitor during and at the end of this study (Fig. 2).

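### The printed HOMA-B equation does not group FBS − 63, so it turns negative below a fasting insulin of 17.5 to 21.9 µU/mL; fasting glucose is also labelled mg/mL where only mg/dL fits

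*Protocol article*

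**What the plan says.** All places are in the protocol article.

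- **Assessments and measurements.** The text introduces the two indices with "The HOMA-IR and HOMA-B will be determined according to suggested formulas [29" and prints both equations. The core of the HOMA-B line reads, in the article's markup, "360/\mathrm{FBS}\ \left(\mathrm{mg}/\mathrm{ml}\right)-63". The only brackets around the arithmetic enclose the whole expression, and nothing groups FBS with 63. HOMA-IR is printed as FBI × FBS divided by 405. In both equations FBI is in µU/mL and FBS in mg/ml.
- **Inclusion criteria.** "FBS 100–125 mg/mL".
- **Study design.** "diagnosed with prediabetes (fasting glucose 100–125 mg/mL) will be screened for enrolment in the study".
- **Study participants.** The same range and unit appear twice, the second time for "women who have been confirmed as having prediabetes (fasting glucose 100–125 mg/mL) and hypovitaminosis D".
- **Objectives and Secondary outcomes.** HOMA-B is a named glucose index to be compared between the four groups and within each group. Glycemic indices other than FBS are secondary outcomes.
- **Statistical analysis.** Continuous variables that are not normal are to be transformed by logarithm, square root, cube root or reciprocal.

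The article nowhere gives FBS in mg/dL, a second HOMA-B formula, or any fasting insulin value.

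**The concern.** By the normal order of operations the printed HOMA-B line divides first and subtracts 63 last. For FBS in the eligible range this gives a negative percentage of beta-cell function over a wide span of insulin values, and such a value has no meaning. The equation is the only computing rule shown for this outcome.

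The fault is not a constant shift that would cancel in a comparison. The printed and grouped forms respond differently to both insulin and glucose, so an analysis coded from the printed line would misstate the changes within groups and the differences between them. Two of the four listed transformations, the logarithm and the square root, are also undefined for negative values.

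The unit is a second, separate fault in the same equations. A fasting glucose of 100–125 mg/mL equals 10,000–12,500 mg/dL, which no participant can have.

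**Working it through.** **Inputs.** The HOMA-B and HOMA-IR equations come from Assessments and measurements, and the FBS range 100–125 from Inclusion criteria. The insulin values below are illustrative assumptions, because the article gives none. It also states no HOMA value, so there is no figure of its own to reproduce.

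**1. Where the printed form changes sign.** 360 × FBI/FBS − 63 < 0 when FBI < 63 × FBS/360.

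- FBS 100: 63 × 100/360 = 17.5 µU/mL
- FBS 110: 63 × 110/360 = 19.25 µU/mL
- FBS 125: 63 × 125/360 = 21.9 µU/mL

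Every eligible woman with FBI below 17.5 µU/mL therefore gets a negative value, whatever her FBS. This needs no assumption about the insulin distribution.

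**2. The possible groupings of the same symbols, at FBI 10 and FBS 110.**

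- As printed: 10 × 360/110 − 63 = 32.7 − 63 = −30.3%
- 63 grouped with 360/FBS: 10 × (360/110 − 63) = 10 × (3.27 − 63) = −597%
- 63 grouped with FBS: 3600/(110 − 63) = 3600/47 = 76.6%

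Only the third is positive for every eligible woman, because FBS − 63 is at least 37.

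**3. Spread.** For FBI 5 to 15 and FBS 100 to 125:

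| Form | Lowest (FBI 5, FBS 125) | Highest (FBI 15, FBS 100) |
|---|---|---|
| Printed | 360 × 5/125 − 63 = −48.6% | 360 × 15/100 − 63 = −9.0% |
| Grouped | 1800/62 = 29.0% | 5400/37 = 145.9% |

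**4. Effect on contrasts.**

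- One µU/mL more insulin at FBS 110: printed 360/110 = 3.3 points; grouped 360/47 = 7.7 points.
- FBS falling from 110 to 105 at FBI 10: printed 34.3 − 32.7 = 1.6 points; grouped 3600/42 − 3600/47 = 85.7 − 76.6 = 9.1 points, nearly six times as much.

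**5. How many women would be negative.** This needs an assumed distribution. Here FBI is taken as log-normal with a log-SD of 0.3 to 0.7, and FBS as uniform on 100–125.

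| Assumed median FBI (µU/mL) | Share negative |
|---|---|
| 10 | 83–99% |
| 15 | 65–81% |
| 22 | 36–44% |
| 25 | 22–37% |

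The share passes one half at a median of about 19.7, which is 63 × 112.5/360 at mid-range FBS.

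**6. Units.** Take 110 mg/dL, which is 1.10 mg/mL, at FBI 10.

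- HOMA-IR with 110: 10 × 110/405 = 2.72. With 1.10: 10 × 1.10/405 = 0.027, which is 100 times too small.
- Printed HOMA-B with 1.10: 3600/1.10 − 63 = 3,210%.
- Grouped HOMA-B with 1.10: 3600/(1.10 − 63) = −58%.

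Only the grouped form with FBS in mg/dL gives sensible values, so the bracket and the unit must be corrected together.

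**The case against.** The strongest defence is that both faults are misprints that nobody will act on. The equation restates a cited source, the article shows no analysis syntax, a negative percentage would be conspicuous, and the Statistical analysis section promises a plausibility check. HOMA-B is one of many secondary measures and can be recalculated from FBS and FBI without loss of data. These points limit the seriousness. They do not make the printed rule right: the plausibility check is not directed at derived variables, and no other specification is shown. Extraction damage is an unlikely explanation, since the brackets in the equation are intact and the fraction in the sample-size formula survived.

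Three stronger readings are tempting, and the article does not support them.

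- **A reader might infer that most participants would have a negative HOMA-B.** That depends on an insulin distribution that the article does not give. It holds only if the median is below about 19.7 µU/mL.
- **A reader might add the negative values and the 100-fold unit error together.** They are alternatives. The printed form goes negative when FBS is entered as 100–125, and then the mg/mL label does no numerical harm. If glucose is really converted to mg/mL, the printed form gives huge positive values. No such conversion is planned.
- **A reader might conclude that the unit compromises enrolment or the primary outcome.** The literal range is impossible, so the slip exposes itself, and no woman is shown to be wrongly included or excluded. The FBS means in the Sample size section, 86.8 and 94.6, are on the same numeric scale as 100–125.

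It is also fair to object that a non-normal HOMA-B could still be transformed: the cube root is defined for negative values. The reciprocal is defined away from zero but does not keep the order of values across it. Only the logarithm and the square root fail outright.

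**Conclusion.** The point holds as a fault in the stated computing rule for one secondary outcome. With FBS entered as 100–125, the printed HOMA-B is negative for any eligible woman with fasting insulin below 17.5 to 21.9 µU/mL, depending on her FBS. That follows from the equation and the entry range alone. The example of −30.3% against 76.6% uses illustrative values. Wrong results and contrasts follow only if the analysis is coded from the printed line.

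The mg/mL label is a subordinate correction. It appears everywhere the article gives a unit for FBS, but it changes numbers only if someone converts glucose to that unit.

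The primary outcome analysis and the sample size are unaffected, and HOMA-B can be recomputed at any time from FBS and FBI. The point is moderate: correct it before the analysis, but it does not threaten the trial's main conclusion. That 63 belongs with FBS in the denominator is inferred from sign and plausibility, because reference 29 was not available.

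**What to change.** 1. In Assessments and measurements, write HOMA-B (%) = 360 × FBI (µU/mL) / (FBS (mg/dL) − 63) and HOMA-IR = FBI (µU/mL) × FBS (mg/dL) / 405, after reconciling both with reference 29.
2. Change mg/mL to mg/dL for FBS in Study design, Inclusion criteria, Study participants (twice) and both HOMA equations.
3. Before the analysis, check the syntax for the derived variables against one worked example, such as FBI 10 µU/mL and FBS 110 mg/dL, which should return HOMA-B 76.6% and HOMA-IR 2.72.

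The cost is a text correction and, if the printed line has already been coded, one line of syntax. No new data are needed.

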**Methods/design:**

This 2 × 2 factorial, triple-blind, randomized, placebo-controlled, clinical trial will be done on 168 women of reproductive age diagnosed with prediabetes and hypovitaminosis D. Participants will be randomly assigned equally to four groups: (1) 1000 mg omega-3 fatty acid twice a day + vitamin D placebo every two weeks; (2) omega-3 fatty acid placebo twice a day + 50,000 IU vitamin D every two weeks; (3) 1000 mg omega-3 fatty acid twice a day + 50,000 IU vitamin D every two weeks; (4) omega-3 fatty acid placebo twice a day + vitamin D placebo every two weeks for eight weeks. At the beginning, participants will provide a self-reported questionnaire on the sociodemographic characteristics. At baseline and post-intervention visits, physical activity, Depression Anxiety Stress Scale 21 and Pittsburgh Sleep Quality Index, and a three-day food record will be collected for each individual. Blood pressure, weight, height, and waist circumference will also be measured.

At the beginning and at the end, a blood sample will be used for estimating serum glucose indices (fasting blood sugar and insulin, homeostasis model assessment-insulin resistance, homeostasis model assessment-beta cell function), lipids (triglyceride, low-density lipoprotein cholesterol, high-density lipoprotein cholesterol, total cholesterol), and vitamin D status.

Data analysis using Kolmogorov–Smirnov test, paired t-test, one-way analysis of variance, and repeated measures analysis of variance will be conducted through SPSS-24 software.

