### Objectives

Compare the mean serum lipid (triglycerides [TG], total cholesterol [TC], low-density lipoprotein cholesterol [LDL-C], high-density lipoprotein cholesterol [HDL-C]) and glucose indices (fasting blood sugar [FBS], fasting blood insulin [FBI], homeostasis model assessment - insulin resistance [HOMA-IR], homeostasis model assessment - beta cell function [HOMA-B]) between the four groups and within each group, before and after intervention.Compare the means of anthropometric indices (weight, waist circumference, body mass index [BMI]) and systolic and diastolic blood pressures between the four groups and within each group, before and after the intervention.Compare the mean scores of the Depression Anxiety Stress Scale (DASS-21) and Pittsburgh Sleep Quality Index (PSQI) between the four groups and within each group, before and after intervention.Determine the relationship between changes in mean level of serum vitamin D and each of the glucose indices, serum lipids, and the mean scores of the DASS-21 and PSQI between the four groups and within each group, during intervention.

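### Read plainly, BMI change is computed from a height re-measured at week 8, which adds avoidable noise to one secondary outcome; one baseline height would remove it

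*Protocol article*

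**What the plan says.** Under Study participants, anthropometry is defined to include height: "Anthropometry including weight, height, and waist circumference will be measured using a digital scale, stadiometer, and non-elastic tape, respectively". The same section says that "anthropometric measurements and measuring blood pressure, will be repeated after eight weeks" and makes no exception for height. The Abstract (Methods/design) also lists height with the measurements made at the baseline and post-intervention visits: "Blood pressure, weight, height, and waist circumference will also be measured".

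Assessments and measurements opens its list with "Then, at the beginning and eight weeks after the intervention, the following will be done". Within that list:

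- Weight is taken "weight without shoes, with minimal clothing, and with a 100-g accuracy".
- Height is taken "height without shoes, standing, heels against the wall, flat and forward head, and with 0.5-cm accuracy".
- "BMI will be calculated using the height and weight measurements".

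No section says that baseline height is carried forward to week 8.

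BMI is one of the anthropometric indices that the Objectives compare before and after treatment, within and between the four groups. Change in anthropometric indices is a secondary outcome. Statistical analysis plans paired t-tests within groups and repeated measures ANOVA between groups.

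**The concern.** Adult height hardly changes in eight weeks, so a difference between a woman's two height readings is almost entirely measurement error. Because BMI divides by height squared, a small relative error in height gives about twice that relative error in BMI, with the opposite sign. Recalculating BMI from a fresh height therefore mixes weight change, which is what the outcome is meant to reflect, with height re-reading error. Weight is read to 0.1 kg, but a half-centimetre difference in height moves BMI as much as several such steps.

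At stake are the precision of the BMI comparison and agreement between BMI and weight in the same woman. If height readings shifted systematically between visits, the before-after tests within groups would move as well.

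**Working it through.** The article states no figure for BMI change, so there is none to reproduce.

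**Inputs from the article:** height accuracy 0.5 cm; weight accuracy 0.1 kg; BMI below 30 kg/m² and age 15 to 50 at entry; 38 women per group before attrition.

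**Assumed inputs, not in the article:** height mean 160 cm, SD 6 cm; BMI uniform from 21 to 30; height-error SD 0.1 to 0.5 cm per reading, recorded to the nearest 0.5 cm; SD of eight-week weight change 1.0, 1.5 or 2.0 kg.

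**1. One record, weight unchanged at 64.0 kg**

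- Baseline, height 160.0 cm: BMI is 64.0 kg divided by (1.600 m)², which is 25.00 kg/m².
- Week 8, height 160.5 cm: BMI is 64.0 kg divided by (1.605 m)², which is 24.84 kg/m².
- Apparent change: a fall of 0.16 kg/m².
- Equivalent weight: 25 kg/m² times the difference between (1.605 m)² and (1.600 m)², which is 0.40 kg, four steps of the scale.

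Across heights of 150 to 170 cm and BMI of 22 to 29.9, a 0.5-cm difference moves BMI by about 0.13 to 0.20 kg/m², equivalent to 0.33 to 0.51 kg.

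**2. The same record with a 0.3 kg gain**

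- Week-8 height: 64.3 kg divided by (1.605 m)² is 24.96 kg/m², a change of -0.04 from the baseline value.
- Baseline height: 64.3 kg divided by (1.600 m)² is 25.12 kg/m², a change of +0.12 from the baseline value.

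**3. Across women (simulation of 2 million women)**

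The variance ratio is var(BMI change, visit-specific height) / var(BMI change, baseline height). It is close to 1 + (SD of false change / SD of BMI change at fixed height)².

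| Height-error SD per reading (cm) | Two heights differ | SD of false BMI change (kg/m²) | Variance rise, weight-change SD 1.0 kg | Variance rise, SD 1.5 kg | Variance rise, SD 2.0 kg |
|---|---|---|---|---|---|
| 0.1 | 23% | 0.08 | 4% | 2% | 1% |
| 0.2 | 43% | 0.11 | 8% | 4% | 2% |
| 0.3 | 58% | 0.15 | 15% | 7% | 4% |
| 0.5 | 73% | 0.24 | 36% | 16% | 9% |

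Hand check of the cell for 0.3 cm and 1.0 kg: the SD at fixed height is 1.0 kg divided by (1.60 m)², which is 0.39 kg/m², and one plus the square of the ratio of 0.15 to 0.39 is 1.15.

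At a weight-change SD of 1.0 kg, BMI change and weight change have opposite signs in about 6%, 9% and 15% of women for error SDs of 0.2, 0.3 and 0.5 cm.

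**4. Effect on a group comparison**

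Take 38 per group, error SD 0.3 cm and weight-change SD 1.0 kg. The unadjusted 95% half-width for a between-group difference is 1.96 × 0.3906 × √(2/38) = 0.176 kg/m² with fixed height. It becomes 0.176 × √1.15, about 0.188, with re-measured height. The Bonferroni multiplier widens both in the same proportion.

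**5. A systematic shift**

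If every week-8 height read 0.5 cm higher, mean BMI would fall by about 0.16 kg/m² in every group. That moves each within-group paired test. It cancels in differences between groups.

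**The case against.** The strongest objection is that the rule is not written down. The article does not say which visit's height enters week-8 BMI, and such a derivation could sit in a full protocol or analysis plan that is not shown. The schedule in Fig. 2 cannot be seen either. This lowers certainty but does not remove the point. The article itself fixes the repeat measurement, its accuracy and the derivation of BMI inside one twice-performed list, and nothing carries baseline height forward.

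The 0.5-cm figure might be an instrument tolerance and not a recording step. The simulated rounding depends on that reading. With uniform errors of ±0.25 cm and no rounding, the variance rise is only 3% at a weight-change SD of 1.0 kg, which lies just below the low end of the range given.

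It is also fair that little hangs on this. The trial is sized on fasting blood sugar, and BMI is one of many secondary outcomes. Weight is analysed in its own right, free of this error, and with a fixed height BMI change is essentially rescaled weight change. Since entry begins at age 15, visit-specific height is not simply wrong for every participant.

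A reader might infer two stronger things, and neither is supported. The first is that BMI change can reverse sign with no change in weight. At constant weight the correct change is zero, so there is no sign to reverse; a reversal needs a small real weight change, as in step 2. Reversals also concern individual records, while the analysed quantity is a group mean, in which random height errors average out. The second is that treatment comparisons are biased. Allocation is randomised and the investigators and participants are blinded, so nothing in the article suggests that height error differs by arm.

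**Conclusion.** The point holds as a minor, inexpensive improvement. On the plain reading, BMI change carries height re-reading error that serves no purpose and can disagree with weight change in individual women. The consequence is some loss of precision for one secondary outcome, without bias between arms: a variance rise of about 4-36%, 2-16% or 1-9% at weight-change SDs of 1.0, 1.5 or 2.0 kg. The upper ends require a height-error SD of 0.5 cm. These ranges rest entirely on assumed error and weight-change SDs and on rounding to 0.5 cm. The within-group tests would be affected systematically only if height readings shifted between visits, and the article gives no sign that they would. The primary outcome and the weight analysis are untouched.

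**What to change.** In Assessments and measurements, add: *BMI at both visits will be calculated from the height measured at baseline and the weight measured at that visit.* Week-8 height can be dropped or kept only as a data check. BMI change is then exactly zero when weight is unchanged and always has the sign of the weight change.

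The cost is one sentence and one derivation line. No new data are needed, and if both heights have already been collected the rule can be applied when BMI is derived. The one downside is that true growth over eight weeks in the youngest participants is ignored; the article gives no figure for it.
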